## Abstract

**Background:**

Myopia is increasingly prevalent worldwide, with projections indicating that nearly 50% of the global population may have myopia by 2050. This surge poses significant concerns due to its impact on vision and quality of life and its link to a range of blinding diseases, including myopic macular degeneration, glaucoma, and retinal detachment. Current pharmacologic and optical interventions offer limited effectiveness in slowing myopia progression, highlighting the urgent need for more effective treatments.

**Objective:**

This study aims to examine the combined effect of bright light therapy and low-dose atropine on myopic progression.

**Methods:**

This is a single-site, 2-arm, single-masked (examiner-masked) randomized controlled trial to compare the effectiveness of low-dose atropine alone and its combination with bright light therapy in retarding myopia progression. The study protocol has been approved by the institutional review boards of Hong Kong Polytechnic University (HSEARS 20180829002-05) and the University of Hong Kong and Hospital Authority Hong Kong West Cluster (UW 20-362). Schoolchildren with myopia aged 7 to 12 years who have not undergone any previous myopic control intervention will be recruited and randomly allocated into 2 groups (n=67 per group) after baseline measurements. Both groups will receive 0.01% atropine twice daily for 24 months. The combination treatment group will also receive a high-intensity lamp for bright light therapy. The primary and secondary outcome measures will be the changes in cycloplegic autorefraction in spherical equivalent refraction and axial length, respectively, measured every 6 months over 2 years from baseline.

**Results:**

The project was funded in January 2019. The recruitment process started on March 21, 2023, and was completed on February 2, 2024. Data collection is expected to be completed in April 2026.

**Conclusions:**

This study will provide new information on whether the combination of bright light therapy and low-dose atropine is more effective than atropine alone in slowing down myopia progression. It will also assess the effectiveness of low-dose atropine used twice daily. Combining bright light therapy and atropine could become a new treatment option if shown to be effective. New data on the effectiveness of using atropine twice daily might also expand available treatment options.

## Introduction

Myopia has become increasingly prevalent worldwide, particularly among children in the Asian region. It has been predicted that almost 50% of the world’s population will have myopia by 2050 [1]. This rapid rise in myopia is alarming not only because of its impact on vision and quality of life [2] but also because of its association with a higher risk of developing a range of blinding diseases later in life, including myopic macular degeneration, glaucoma, and retinal detachment [3].

Previous studies have identified pharmacologic and optical methods to retard myopia progression that only have a low to moderate effectiveness [4]. Thus, there is still an urgent need to explore innovative treatment approaches that are more capable than current methods. One promising approach is bright light therapy. Outdoor illumination in direct sunlight can reach up to 100,000 lux, whereas indoor illumination typically ranges from 100 to 500 lux [5]. One hypothesis explaining the rising prevalence of myopia among schoolchildren is that urban populations have embraced a lifestyle that limits exposure to bright outdoor light [6]. Research on animals (chicks, mice, and rhesus monkeys) has demonstrated that exposure to bright light ranging from 15,000 to 40,000 lux can entirely inhibit the development of myopia [7-10]. Observational clinical studies have indicated that an increase in time spent outdoors is associated with a more hyperopic refractive error and a lower incidence of juvenile-onset myopia [11,12]. In addition, a 1-year-long randomized clinical trial by Wu et al [13] has shown that an increase in outdoor activity can lead to less myopic shift and axial elongation in both children with and without myopia. The protective effect against myopia does not appear to be due to physical exercise, as indoor exercise does not inhibit myopia [14].

While it is clear that spending more time outdoors is beneficial for preventing and controlling myopia, the next clinically relevant question is whether artificially applied bright light indoors could achieve the same effect. Therefore, our team has designed a randomized controlled study to investigate the effect of bright light therapy (approximately 10,000 lux) on myopia [15]. This innovative approach will also be examined to explore the effect of its combination with low-dose atropine.

As no current treatment has been found to be able to completely halt myopia progression, another option is the potential use of a combination treatment. It is hypothesized that bright light therapy could provide additive efficacy to slow myopia progression when used in combination with low-dose atropine. Low-dose atropine has demonstrated a dose-dependent effect on slowing myopia with minimal side effects [16]. This combination is promising as there are preliminary data suggesting that these 2 therapies work on different mechanisms. While the exact mechanism for atropine’s action is still unknown, it is thought to affect the development of myopia mainly by acting as a reversible competitive antagonist of acetylcholine muscarinic receptors that are found in many parts of the eye [17]. Regarding bright light therapy, its inhibitory effect on myopia is suggested to be mediated by the retinal dopaminergic pathways [18].

On the basis of these rationales, this clinical trial was designed to examine the combined effect of bright light therapy and low-dose atropine on myopic progression. The primary aim of this trial is to investigate whether the combination treatment with bright light therapy and low-dose atropine would be more effective than atropine alone. This trial will also assess the effectiveness of low-dose atropine in slowing myopia progression. Factors associated with the effectiveness of the treatments will also be identified. In addition, compliance and participant acceptability (particularly in terms of visual performance) of the combination therapy will be evaluated.

## Methods

### Study Design and Setting

This protocol describes a single-site, 2-arm, single-masked (examiner-masked) randomized controlled trial comparing the effectiveness of low-dose atropine alone and in combination with bright light therapy in retarding myopia progression. This manuscript is based on protocol version 1.6 (September 2022). This study will last for 2 years and is an auxiliary study to a previous study (phase 1 study) [15] conducted by the same team sharing the same study design except for the choice of treatment. The phase 1 study [15] will consist of 1 control group and 2 treatment groups, whereas this phase 2 study will consist of 2 treatment groups only. This paper will only describe the design of the phase 2 study, and details of the intervention for each group are shown in Figure 1 [15]. The investigation will be separated into 2 phases due to logistical issues. Participants from the phase 1 study will not continue into the phase 2 study. This study consists of 2 arms: atropine and atropine combined with bright light therapy. Participants will be randomized to the 2 treatment groups at a ratio of 1:1 using an age-stratified simple randomization. Data from the 2 phase 2 treatment groups will be compared with each other, and comparisons with phase 1 data will be conducted for exploratory analysis. Identical inclusion criteria will be used for both studies to minimize potential selection bias. The application of consistent methodologies and statistical approaches will enable meaningful comparisons across interventions.

**Figure 1. F1:**
[figure not shown]
Intervention groups in the phase 1 and phase 2 studies. The protocol for the phase 1 study has been published elsewhere [15]. This paper only describes the design of the phase 2 study.

All data collection will take place at the Optometry Research Clinic of Hong Kong Polytechnic University or the HKU Eye Centre, Department of Ophthalmology, University of Hong Kong. This trial protocol is reported in accordance with the SPIRIT (Standard Protocol Items: Recommendations for Interventional Trials) guidelines [19].

### Ethical Considerations

This study protocol meets the tenets of the Declaration of Helsinki and has been approved by the institutional review boards of Hong Kong Polytechnic University (HSEARS 20180829002-05) and the University of Hong Kong and Hospital Authority Hong Kong West Cluster (UW 20-362). Written consent from the participants and their parents and assent from the participants will be obtained by examiners before any study procedures are performed. The study was prospectively registered at ClinicalTrials.gov (NCT04923841) on June 11, 2021. All procedures will adhere to the good clinical practice guidelines. Study personnel, including administrative staff and investigators, will complete the good clinical practice certification course. Patients and members of the public were not involved in the design, conduct, reporting, or dissemination planning of this research. After publication, parents or guardians and participants will be informed of the study results via a newsletter. This paper does not contain any individual identifiable data.

### Sample Size Calculation

The sample size is estimated based on the 2-year change in refractive error in the 0.01% atropine treatment group (−0.64, –0.44 to +0.44 D) from a previous myopia control study [20]. Assuming that, over 2 years, combination treatment is more effective than 0.01% atropine alone by 0.25 D, which is considered a clinically significant change, 56 participants per group will be required. This sample size will enable the demonstration of a statistically significant difference between the 2 groups at a 5% significance level with 85% power. The sample size for each study arm will be adjusted to 67 per arm assuming a 20% loss to follow-up. As a result, a total sample size of 134 participants will be recruited for this study.

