### Statistical Analyses

The latest version of the SPSS software (IBM Corp) will be used for statistical analyses. This study will use the same statistical approach as that used in the previous phase 1 study [15]. Data from the right eyes will be used for analyses. The normality of the data will be examined using the Kolmogorov-Smirnov test. Demographic and optometric data will be presented as means and SDs or as numbers and percentages as appropriate. The chi-square test (or, if appropriate, the Fisher exact test) and one-way ANOVA will be performed to compare baseline between-group differences in demographics (age and sex). Changes in primary, secondary, and other outcomes at different time points will be analyzed using a mixed-effects model for repeated measures, which includes fixed effects for the treatment group, time, the interaction between group and time, and covariates including age and baseline myopia. If statistically significant differences in baseline demographic characteristics between arms are found, these will also be adjusted for.

The progression of myopia over 2 years will be calculated as the difference in cycloplegic autorefraction in spherical equivalent refraction and axial length between the baseline and the 2-year visit. The relative treatment effect in each arm will be determined by dividing the difference in myopia progression between the treatment group and the control group in the phase 1 study [15] by myopia progression in the control group and then multiplying by 100%. Additionally, the absolute treatment effect [29] will be presented to facilitate comparison with other studies. Multiple regression analysis will be used to identify factors associated with myopia control effectiveness.

All analyses will follow the intention-to-treat approach. Missing values of outcome variables and covariates will be replaced using a multiple imputation procedure with 10 sets of imputations assuming missingness at random. Sensitivity analyses for the primary outcomes include (1) complete-case analysis and (2) per-protocol analysis. All analyses will be 2-tailed, with a significance level of 5%.

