## Discussion

This 2-arm randomized controlled trial will be the first to investigate the combined effect of bright light therapy and low-dose atropine on myopia progression in schoolchildren. We hypothesized that bright light therapy would have an additive effect on slowing myopia progression when combined with low-dose atropine. If proven effective, this combination treatment could represent a novel therapeutic strategy. Combination treatment, also known as polytherapy, has emerged as a new approach in recent years. The rationale for its use is that there may be an additive effect on treatment efficacy if the treatment of choice affects myopia pathogenesis through distinct mechanisms. A recent meta-analysis suggests that combination treatment is the most effective intervention for myopia control [30]. Both Tan et al [31] and Kinoshita et al [32] have shown that the combination of 0.01% atropine and orthokeratology is more effective than orthokeratology alone in slowing axial elongation. As the proposed myopia control mechanisms differ between atropine and bright light therapy, this randomized clinical trial is designed to investigate whether combining these 2 promising therapies results in an additive effect.

Additionally, bright light therapy has not yet been studied for its effectiveness in controlling myopia progression. Therefore, our results will contribute valuable insights to the literature regarding its potential efficacy. Another feature of this study is the administration of low-dose atropine twice daily. At the time of writing, all other randomized clinical trials [20,33-40] using low-dose atropine to control or prevent myopia only administered the treatment once daily. It has been repeatedly shown that 0.01% atropine is a safe and well-tolerated treatment but is limited in its effectiveness [34]. Increasing the concentration of atropine would lead to a stronger myopia control effect [34], but unfortunately, both the risk of adverse effects [34] and the extent of the rebound effect are dose dependent [38]. Administering atropine twice daily provides a more prolonged presence of the medication, which could result in a stronger myopia control effect without significantly increasing the risk of adverse events.

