A recent 1-year–long randomized clinical trial by He et al [41] provides supporting evidence for this hypothesis. In their study, the axial elongation and spherical equivalent refraction progression in the twice-daily group (n=36) were 34% and 53% lower, respectively, than in the once-daily group (n=34). There were no clinically significant differences between the 2 groups in safety parameters, including accommodation amplitude, pupil diameter, and intraocular pressure. The study proposed in this paper, with a larger sample size and longer follow-up, will provide additional insights into optimizing the balance between efficacy and safety in low-dose atropine treatment for myopia control.

The strengths of this study include its prospective, randomized design and the use of masked examiners. The primary limitation of this study is the lack of masking of participants. The study duration is only 24 months due to budget constraints, so longer-term results will not be available. In addition, while the effectiveness of bright light therapy is examined in this study, further research is still needed to determine the optimal light level. Whether the benefit, if any, would apply to patients with different characteristics also remains to be assessed.

The results of this study will be disseminated at scientific conferences and in peer-reviewed, indexed journals in the fields of optometry and ophthalmology.

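### Minor: the 20% loss allowance multiplies 56 by 1.2 instead of dividing by 0.80, so 67 per arm leaves about 54 completers rather than the required 56

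*Protocol article*

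**What the plan says.** The Sample Size Calculation section of the protocol article starts from a two-year refractive change under 0.01% atropine in an earlier trial, printed as a mean and spread (minus sign before the first figure) of "0.64, –0.44 to +0.44 D". It assumes that "combination treatment is more effective than 0.01% atropine alone by 0.25 D" over two years and concludes that "56 participants per group will be required", "at a 5% significance level with 85% power". It then says: "The sample size for each study arm will be adjusted to 67 per arm assuming a 20% loss to follow-up". The total is given as 134. The Statistical Analyses section sets two-sided testing at 5%, and the randomization is 1:1. No other section gives a different loss rate or another reason for 67.

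**The concern.** A loss rate is a fraction of the children enrolled. The enrolled number must therefore be the required number of completers divided by the fraction expected to remain. Adding 20% of the completers to the completers gives a smaller number. When 20% of that smaller number is lost, the trial falls below its own requirement.

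What is at stake is the accuracy of a power statement that is likely to be carried into the results paper. As printed, 134 children, 20% loss and 85% power are presented as consistent with one another, and they are not.

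**Working it through.** **Inputs.** From Sample Size Calculation: difference 0.25 D, power 85%, significance level 5%, 56 per group before loss, 20% loss, 67 per arm and 134 in total after loss. From Statistical Analyses: two-sided testing. From Randomization and Masking: 1:1 allocation. The SD is not labelled as such; I read it as 0.44 D, which is an assumption supported by step 1.

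**Step 1: reproduce the 56.**

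n = 2 × (z for two-sided 5% + z for 85% power)² × SD² / difference²

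n = 2 × (1.960 + 1.036)² × 0.44² / 0.25² = 55.6, rounded up to 56.

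This matches the plan. The t-test version gives 56.6, so 57. A one-sided test would give 45, 80% power would give 49 and 90% power would give 66, so none of these is what the plan used.

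**Step 2: reproduce the 67.**

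- 56 × 1.2 = 67.2, which gives 67 when rounded down.
- 56 / (1 − 0.20) = 70, or 140 in total.

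Only the multiplication gives 67. The shortfall is 3 per arm and 6 in total (6/140 = 4.3%).

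**Step 3: completers at the stated loss.**

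- 67 × 0.80 = 53.6 per arm (134 × 0.80 = 107.2 in total), against 56 per arm (112 in total) required.
- 70 × 0.80 = 56 exactly.
- Loss at which 67 still leaves 56: 1 − 56/67 = 16.4%, or 11 children per arm.

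**Step 4: power for 0.25 D with SD 0.44 D, two-sided 5%.**

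Normal approximation: power = Φ(0.25 / (0.44 × √(2/n)) − 1.960).

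- n = 53.6: Φ(2.941 − 1.960) = Φ(0.981) = 83.7%.
- n = 56: Φ(3.007 − 1.960) = Φ(1.047) = 85.2%.

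| Completers per arm | Normal approximation | t test |
|---|---|---|
| 53.6 (67 enrolled, 20% lost) | 83.7% | 83.0% |
| 56 (70 enrolled, 20% lost) | 85.2% | 84.6% |

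The comparison must stay within one column: the drop is 1.5 points (normal) or 1.6 points (t test). Setting the t-test 83.0% against the nominal 85% would overstate it, because 56 per arm reaches 85% only under the normal approximation.

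**The case against.** The strongest reply is that the sum describes a simple comparison of completers, which is not the planned primary analysis. The Statistical Analyses section specifies a mixed model for repeated measures adjusted for age and baseline myopia, analysed by intention to treat with multiple imputation; complete cases are only a sensitivity analysis. To bring 53.6 per arm back to the power of 56, the residual variance need fall only by 1 − 53.6/56 = 4.3%. Covariates could plausibly supply that, although the article gives no figure for how much variance they explain. An SD of 0.43 D instead of 0.44 D would do about the same (0.43²/0.44² = 0.955). This stands as a limit on the consequence. It does not rescue the printed figures, because the sample size section takes no credit for the model.

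A reader might also go further and infer that the whole calculation rests on the wrong control arm. The Discussion lists the source trial for the −0.64 D figure among those that "only administered the treatment once daily", whereas both arms here are dosed twice daily. It also cites a trial in which axial elongation and refractive progression under twice-daily dosing "were 34% and 53% lower, respectively, than in the once-daily group". From that one could argue that little progression remains for light therapy to slow, and that 0.25 D is out of reach. The documents do not support this as an error, for three reasons:

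- The control mean does not enter the formula in step 1; only the difference and the SD do, so 56 is unchanged.
- The 0.25 D is justified as an absolute difference of clinical importance, and the stated hypothesis is an additive effect. No relative target is given that would shrink with the control mean.
- Applying the 53% to this trial would carry a one-year ratio from 36 and 34 children over to a two-year mean from a different study. The article offers that trial as supporting evidence, not as a planning value.

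**Conclusion.** The sample size paragraph is wrong as written, and the error is minor. With 20% loss, the stated requirement of 56 completers needs 70 per arm; 67 leaves about 53.6. The cost is about 1.5 points of power for 0.25 D, before any gain from the adjusted repeated-measures model. This rests on reading the SD as 0.44 D, on loss being counted as a share of those enrolled, and on equal loss in both arms.

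It should not be read as serious underpowering. Power stays at about 83–84% at the assumed loss, and if loss turns out to be 16% or less the 56 completers are there.

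**What to change.** Recruitment was completed on February 2, 2024, so correct the statement rather than the enrolment. Either of these would do:

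- *With 67 children per arm, 56 completers per arm, and so 85% power (normal approximation), are retained for a loss to follow-up of up to about 16%.*
- *With 67 children per arm and 20% loss to follow-up, power to detect 0.25 D is about 83–84%, before any gain from the covariate-adjusted repeated-measures model.*

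In the same sentence, label 0.44 D as the SD if that is what it is. The results paper should carry the corrected statement. The cost is wording only: a slightly less favourable power or tolerated-loss figure, with no extra participants and no change to treatment, outcomes or analysis.

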### Inclusion Criteria

Children meeting the following criteria will be included:

Children who are Hong Kong ChineseMyopia (spherical equivalent) of −0.75 D to −5.00 D in both eyesAge at enrollment of 7 to 12 yearsAstigmatism and anisometropia of 1.50 D or lessSpectacle-corrected monocular visual acuity of 0.04 logMAR or better in both eyesNormal binocular functionParents’ understanding and acceptance of the random allocation of grouping and maskingAbility to wear the prescribed spectacles, apply eye drops, and undergo light therapy daily

### Exclusion Criteria

Children meeting the following criteria will be excluded:

Eye disease or binocular vision problems (eg, strabismus, amblyopia, oculomotor nerve palsies, or corneal disease)Previous intraocular or corneal surgeryOcular or systemic disease that may affect vision function or development (eg, endocrine, cardiac, and respiratory diseases; diabetes; or Down syndrome)Allergy to atropinePrevious or current use of gas-permeable, soft bifocal, or orthokeratology contact lenses or bifocal, progressive addition lenses; specific myopic control spectacle wear; or use of atropine or pirenzepine (longer than 1 month)Previous or current participation in myopia control studies

